## Abstract

Recurrent glioblastoma (GBM) remains a therapeutic challenge with poor prognosis and limited treatment options. This phase I, open-label, dose-escalation trial investigates the safety and tolerability of combining sulfasalazine, a cystine/glutamate antiporter-inhibitor, with gamma knife radiosurgery (GKRS) for patients with recurrent GBM. Sulfasalazine is hypothesized to potentiate radiotherapy by depleting tumor cells of glutathione (GSH), thereby enhancing susceptibility to reactive oxygen species generated during irradiation. The study aims to establish the maximum tolerated dose (MTD) of sulfasalazine in combination with GKRS and explore preliminary efficacy signals through imaging and clinical endpoints.•Primary objective: Determine the MTD of sulfasalazine combined with GKRS and recommend a dose for future•phase II trials using the common toxicity criteria for adverse events v4.0.•Secondary objectives: Assess changes in intratumoral GSH via GSH‑edited Magnetic Resonance Spectroscopy, tumor response by Response Assessment in Neuro‑Oncology criteria, metabolic response on Carbon-11 methionine positron emission tomography, quality of life, progression free and overall survival.•Design: Open-label, dose-escalation study enrolling 12–24 patients with recurrent GBM eligible for GKRS.Patients receive sulfasalazine for 3 days prior to GKRS, followed by 12 months of monitoring for adverse events, imaging biomarkers, radiological and survival outcomes. This trial will provide safety data and inform the potential of sulfasalazine as a radiosensitizer in GBM treatment.

Primary objective: Determine the MTD of sulfasalazine combined with GKRS and recommend a dose for future

phase II trials using the common toxicity criteria for adverse events v4.0.

Secondary objectives: Assess changes in intratumoral GSH via GSH‑edited Magnetic Resonance Spectroscopy, tumor response by Response Assessment in Neuro‑Oncology criteria, metabolic response on Carbon-11 methionine positron emission tomography, quality of life, progression free and overall survival.

Design: Open-label, dose-escalation study enrolling 12–24 patients with recurrent GBM eligible for GKRS.

## Specifications table

**Table utbl0001:** 

Subject area	Medicine and Dentistry
**More specific subject area**	Radiosensitization for glioblastoma recurrence
**Name of your protocol**	Phase I trial combining sulfasalazine and gamma knife radiosurgery for recurrent glioblastoma
**Reagents/tools**	Sulfasalazine EN «Pfizer», Gamma knife (Elekta Icon)
**Experimental design**	Open label phase I 3 + 3 dose escalating design
**Trial registration**	ClinicalTrials.gov Identifier: NCT04205357
**Ethics**	The trial was approved by the regional ethical committee (REK vest 6834) and the European Medicines Agency (EUDRACT No.2019–002,110-40). Informed consent was obtained from all trial participants.
**Value of the Protocol**	• Introduces a novel radiosensitization strategy by targeting tumor redox homeostasis through cystine/glutamate antiporter system x_C_^−^ inhibition, addressing a key radioresistance mechanism in glioblastoma. • Provides first-in-human safety and tolerability data for sulfasalazine combined with stereotactic radiosurgery, alongside patient reported quality of life assessments. • Offers mechanistic evidence of treatment effect through glutathione‑edited Magnetic Resonance Spectroscopy) and preliminary efficacy data via Carbon-11 methionine positron emission tomography and Magnetic Resonance imaging.

## Background

Glioblastoma (GBM) is the most common malignant primary brain tumor in adults, with an incidence of 3–4 per 100,000 and a median age at diagnosis of 65 years[1]. Despite multimodal treatment with surgical resection, high dose radiotherapy, and temozolomide, GBM remains incurable, and recurrence is inevitable[2]. At recurrence the therapeutic options are limited, and there is no established standard of care. Management is largely palliative, balancing potential benefits with quality of life (QoL).

Current strategies for recurrent GBM include re-resection, systemic chemotherapy, bevacizumab, tumor treating fields and conventional re-irradiation or stereotactic radiosurgery (SRS). *Re*-resection is feasible in only 20% of cases and carries significant morbidity[3]. Resistance to temozolomide develops rapidly. Lomustine[4], bevacizumab[5], and tumor treating fields[6] have shown limited efficacy. Although conventional fractionated radiotherapy is the most effective part of the initial treatment[7], it is rarely repeated at recurrence due to the risk of neurocognitive side effects, making SRS an attractive alternative. SRS delivers single session high-dose, focal radiation to recurrent tumors while sparing surrounding brain tissue, offering a favorable safety profile and efficacy compared to surgery[8], chemotherapy and conventional radiotherapy[9]. Still, the therapeutic impact of SRS is constrained by GBM radioresistance and prior high‑dose radiation exposure. In a retrospective study using an 18 Gy prescription dose, almost half of the patients ultimately required surgical resection due to radiation necrosis[10], highlighting the need for improved radiation strategies.

Radioresistance is in part mediated by antioxidant defenses such as glutathione (GSH)[11]. Tumor cells neutralize radiation-induced reactive oxygen species (ROS), preventing DNA damage and cell death. The cystine/glutamate antiporter system x_C_^−^ (xCT), providing cysteine uptake needed for GSH synthesis[12] is upregulated in several types of cancers[13]. Sulfasalazine, an FDA-approved anti-inflammatory drug, inhibits xCTr[12]. We have previously shown that xCT was minimally expressed in healthy brain tissue and markedly upregulated in 30 GBM biopsies from our institutional tumor bank[14]. Moreover, our preclinical studies demonstrated that sulfasalazine depletes GSH, increases ROS, and synergistically enhances radiation-induced DNA damage in glioma cell lines and significantly prolong survival in a GBM xenograft models when combined with gamma knife radiosurgery (GKRS) compared to either treatment alone[14]. This protocol describes the first-in-human Phase I trial evaluating sulfasalazine as a radiosensitizer in combination with GKRS for recurrent GBM. The study aims to establish the maximum tolerated dose of sulfasalazine, the recommended dose for a future phase II trial and to assess the preliminary efficacy through advanced imaging (GSH‑edited Magnetic Resonance Spectroscopy (GSH‑edited MRS)for GSH depletion, Carbon-11 methionine positron emission tomography ([¹¹C]methionine PET) for metabolic tumor response) as well as clinical outcomes including QoL and survival.

## Description of protocol

### Study rationale

Recurrent glioblastoma carries a dismal prognosis and lacks effective treatment options, creating a clear need for innovative therapeutic strategies. Recurrence typically develops locally at the resection margin, making focal retreatment an attractive approach, however, the effect of GKRS is constrained by prior irradiation and the inherent radioresistance of glioblastoma. Preclinical studies show that short‑term sulfasalazine exposure is sufficient to selectively deplete intratumoral GSH, inhibiting xCT‑mediated cystine uptake and thereby increasing susceptibility to radiation‑induced oxidative stress, prolonging survival without toxicity in experimental models. This selective radiosensitizing effect enhances the radiation response in tumor tissue while sparing normal brain supporting clinical evaluation of sulfasalazine repurposed as a radiosensitizer.

Sulfasalazine has a well-known safety profile with mostly mild gastrointestinal adverse events. However, GBM patients often take multiple concomitant medications and have compromised health status, which could increase their susceptibility to adverse effects. Earlier glioma trials [15,16] using prolonged sulfasalazine dosing reported substantial neurological toxicity in patients with large recurrences and low performance status, or hematologic toxicity when sulfasalazine was administered long‑term together with temozolomide, indicating that a brief sulfasalazine regimen is essential to avoid cumulative drug toxicity. This phase I study therefore evaluates a three‑day sulfasalazine course prior to GKRS using clinically familiar sulfasalazine dosing, a conservative GKRS prescription dose [8], and strict eligibility criteria to minimize patient risk while assessing safety. If the combination is well tolerated and shows early indications of activity, these findings would justify progression to a phase II trial and further development of this treatment approach for recurrent glioblastoma.

### Aims of study

The primary aim of this study is to evaluate the safety of sulfasalazine in combination with GKRS determining the maximum tolerated dose and recommended phase II dose. The secondary aim is to explore preliminary anti‑tumor efficacy, including changes in intratumoral glutathione measured by GSH‑edited MRS; Magnetic Resonance Imaging (MRI)‑based tumor response at planned intervals; progression‑free (PFS) and overall survival (OS); [¹¹C]methionine PET ‑based assessment of metabolic response; patient‑reported QoL; functional status by Karnofsky Performance Status (KPS); corticosteroid use; and associations between prognostic markers and treatment response.

### Study design

This is a phase I, single‑center dose‑escalation trial using a classic 3 + 3 design [17] to evaluate escalating doses of oral sulfasalazine administered for three days prior to GKRS with an anticipated recruitment period of 24 months. The dose will be escalated or de-escalated with diminishing fractions of the preceding dose (modified Fibonacci sequence), depending on the occurrence of adverse events grade ≥ 3.

Cohorts of three patients receive escalating once‑daily sulfasalazine doses (1.5, 3, 4.5, 6 g) for three days, with GKRS on Day 3. Escalation proceeds if no ≥ grade 3 toxicity occurs; a single ≥ grade 3 event expands the cohort to six; ≥2 events at a dose level in 3–6 participants define that dose as exceeding the maximum tolerated dose (MTD), with the preceding dose as the recommended phase 2 dose.

Each participant undergoes a three‑day treatment phase followed by clinical and radiological follow‑up for up to one year. This design allows systematic dose escalation while ensuring patient safety and assessment of early efficacy signals.

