### Sample size

As is standard for phase I dose‑escalation studies using a 3 + 3 design, no formal sample size calculation was performed. The total number of participants is determined by the number of dose‑escalation cohorts required to identify the maximum tolerated dose. Based on the planned four dose levels, the study is expected to enroll between 12 and 24 patients, which is consistent with conventional 3 + 3 methodology and provides an adequate basis for assessing safety and tolerability in this early‑phase setting.

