### Intervention

Participants are admitted to the hospital for five days, from Monday to Friday. Screening procedures and baseline assessments are conducted on the day of admission (Day 0). The intervention takes place over the subsequent three days (Day 1–3), and participants are discharged on Day 4 following an end‑of‑treatment safety evaluation.

During the intervention period, participants receive oral sulfasalazine in the form of enteric‑coated 500 mg tablets administered once daily for three consecutive days. Dose escalation follows a traditional 3 + 3 design, in which cohorts of three to six participants receive one of four predefined dose levels: 1.5 *g*, 3 *g*, 4.5 *g*, or 6 *g* once daily. All doses are administered under the supervision of a study nurse, who monitors intake and assesses acute tolerability.

On the third intervention day, approximately 6 hours after participants receive their third and final sulfasalazine dose, they undergo stereotactic gamma knife radiosurgery. GKRS is delivered with a standard prescription dose of 12 Gy to the contrast‑enhancing tumor volume.

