### Follow‑up assessments

#### Primary outcome

The dose‑limiting toxicity (DLT) window is defined as Day 1 (first dose of sulfasalazine) through 30 days after the final sulfasalazine dose and gamma knife treatment on Day 3 during which adverse events will be recorded continuously. Adverse events will be graded from 1 to 5 according to Common Terminology Criteria for Adverse Events (CTCAE) version 4.0 [19,20]. For each AE, investigators will assign attribution using standard categories (unrelated, unlikely, possibly, probably, or definitely) to determine the causal relationship to sulfasalazine and GKRS. DLT is defined as any CTCAE v4.0 grade ≥ 3 adverse event occurring within this window, assessed by the investigator as at least possibly related to trial intervention. Adverse events considered to be clearly attributable to expected disease progression or pre-planned hospitalization admission (ie, elective or scheduled surgery arranged prior to the start of treatment) will not be reported as DLT. Similarly, treatment‑related effects expected following GKRS (e.g. pseudoprogression or increased peritumoral edema) and events listed in the sulfasalazine SmPC are not considered “unexpected” and are only classified as Suspected Unexpected Serious Adverse Reactions (SUSAR) if more severe in intensity or more frequent than anticipated.

Safety monitoring includes daily clinical evaluations of vital signs and laboratory testing (hematology, renal/hepatic function, electrolytes, C‑reactive protein, and urine analysis) during the 5-day hospitalization (Day 0–4) in conjunction with the 3-day intervention period (Day 1–3) and at outpatient follow‑up visits at 1, 2, and 4 weeks. MRI will be performed on Day 4 and at 4 weeks to detect early edema and other acute treatment‑related changes. The 4‑week visit will also include [¹¹C]methionine PET. Participant‑reported outcomes during the safety monitoring period will be collected using the FACT‑Br questionnaire at Day 0, Day 4, and weeks 1, 2, and 4. KPS will be assessed at the same timepoints.

Dose escalation follows the 3 + 3 design and proceeds only if no participant experiences a treatment‑related CTCAE v4.0 ≥ 3 adverse event. If one participant experiences a grade ≥ 3 event, the cohort will be expanded to six participants. The maximum tolerated dose (MTD) is defined as the dose preceding that at which 2 of 3 or 2 of 6 patients experience a grade 3 or higher adverse event within the DLT-window.

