### Data management and analysis

Study data will be recorded in protocol‑specific case report forms and monitored regularly for completeness, consistency, and accuracy. An independent DMC and steering committee will be appointed to oversee safety and the scientific integrity of the study and ensure adherence to the protocol, respectively.

All datasets will be de‑identified before analysis and stored in secure institutional repositories in accordance with local data‑protection regulations. Statistical analyses will be performed using validated software packages, SPSS and R.

The primary endpoint will be determination of the maximum tolerated dose and the recommended phase II dose of sulfasalazine administered as a radiosensitizer. The number of participants experiencing CTCAE v4.0. grade ≥ 3 adverse events will be summarized within each dose cohort, and formal hypothesis testing will not be required for dose determination.

Secondary endpoints will be summarized using descriptive statistics. Secondary endpoints will have limited statistical power due to small sample size and expected attrition related to disease progression or missed assessments. Time‑to‑event secondary outcomes (FFLP, PFS, OS) will be analyzed using Kaplan-Meier method and Cox models, while longitudinal secondary outcomes (tumor volume, KPS, FACT‑Br, SUVmax, and GSH-edited MRS-levels) will be analyzed using MLMs for repeated measures accommodating incomplete follow‑up under a missing at random assumption.

For tumor volume, KPS, and FACT‑Br, fixed effects will include time and interaction with time, with baseline score, age, and sex as covariates. Both intercept and slope of time will be included in the model as random effect factors. Prespecified pairwise contrasts across time points will use a Šidák adjustment for multiple comparisons. For GSH and SUVmax values, fixed effects will include region (tumor vs. normal‑appearing brain), time relative to baseline, and region by time interactions. .

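### The escalation and MTD rule is stated inconsistently on unit of count (events or participants) and on attribution (related or any cause), so the same data can give different MTDs

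*Protocol article*

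**What the plan says.** All places are in the protocol article.

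- **Study design** makes escalation and de-escalation turn on grade 3 or higher adverse events ("depending on the occurrence of adverse events grade ≥ 3"). For expansion, "a single ≥ grade 3 event expands the cohort to six"; for the MTD, "≥2 events at a dose level in 3–6 participants define that dose as exceeding the maximum tolerated dose (MTD". The unit is the event, and neither relatedness nor a time window is given.
- **Primary outcome** sets a window from Day 1 to 30 days after the last sulfasalazine dose and radiosurgery. It defines a DLT as a grade 3 or higher event in that window, "assessed by the investigator as at least possibly related to trial intervention", and excludes events clearly due to expected progression and pre-planned admissions. Its escalation sentence counts participants and is limited to treatment-related events. Its expansion sentence counts participants but drops relatedness. Its MTD sentence takes the dose below the one at which "2 of 3 or 2 of 6 patients experience a grade 3 or higher adverse event within the DLT-window".
- **DMC oversight** has any grade 3 or higher event after the first review, within the window, trigger a further assessment that may lead to expansion or de-escalation. Relatedness is not mentioned.
- **Data management and analysis** gives the primary summary as the number of participants with such events: "grade ≥ 3 adverse events will be summarized within each dose cohort". It does not say whether these are DLTs or events of any cause.

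**The concern.** A 3 + 3 design has no estimator beyond its decision rule: the rule, applied to cohorts of three to six, is the analysis of the primary endpoint. Here two features of the rule vary with the sentence being read. The first is whether one participant with two qualifying events counts once or twice. The second is whether an event judged unrelated counts at all. Both can occur in this trial. Neutropenia and thrombocytopenia, two of the toxicities the protocol names, can arise in the same participant. The Study rationale section describes patients with compromised health and many concomitant medications, so unrelated grade 3 events are plausible. If the wording is settled only after such events are seen, the MTD depends on a choice made with the data in hand.

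**Working it through.** **The plan's own figure.** Sample size states: "Based on the planned four dose levels, the study is expected to enroll between 12 and 24 patients". Intervention states that "cohorts of three to six participants receive one of four predefined dose levels". Four levels × 3 = 12 and four levels × 6 = 24, so the range reproduces. It is the same under every reading of the rule and does not help choose between them.

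**Same data, different decisions.** Outcomes in the first three participants of a cohort, within the window:

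| Scenario | Study design | Primary outcome, MTD sentence read literally | Primary outcome, DLT definition and escalation sentence |
|---|---|---|---|
| A. One participant has two related grade ≥3 events | 2 events: above MTD | 1 of 3: expand to six | 1 of 3: expand to six |
| B. Two participants have one unrelated grade ≥3 event each | 2 events: above MTD | 2 of 3: above MTD | 0 of 3: escalate |
| C. One related and one unrelated event, in different participants | 2 events: above MTD | 2 of 3: above MTD | 1 of 3: expand to six |

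Scenario A isolates the unit of count. Scenario B isolates attribution and shows that this conflict also lies within the Primary outcome section itself.

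**Size under assumed rates.** The documents give no event rates, so the following are assumptions:

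- p = related grade ≥3 risk per participant = 10%, the same at every level
- s = share of affected participants with two or more such events = 20% to 50%
- u = unrelated grade ≥3 risk per participant = 5%, 10% or 20%, independent of p
- participants are independent, and 1 of 6 is treated as allowing escalation

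A level is passed if nothing counts in the first three, or if exactly one counts there and none in the next three.

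- Participants: pass = (1−p)³ + 3p(1−p)⁵
- Events: pass = (1−p)³ + 3p(1−s)(1−p)⁵
- Any cause: use the participant formula with p replaced by 1 − (1−p)(1−u)
- Stopping somewhere in four levels = 1 − pass⁴

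Worked for participants, related only: 0.9³ + 3(0.1)(0.9⁵) = 0.729 + 0.177 = 0.906. The dose is declared too high with probability 9.4% per level, and 1 − 0.906⁴ = 32.6% over four levels.

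| Reading | Above MTD, per level | Somewhere in four levels |
|---|---|---|
| Participants, related only | 9.4% | 32.6% |
| Events, related only, s = 20% | 12.9% | 42.5% |
| Events, related only, s = 50% | 18.2% | 55.3% |
| Participants, any cause, u = 5% (combined risk 14.5%) | 17.6% | 53.9% |
| Participants, any cause, u = 10% (combined risk 19%) | 27.0% | 71.6% |
| Participants, any cause, u = 20% (combined risk 28%) | 46.4% | 91.8% |

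**After 1 of 6.** One of six is below the threshold for exceeding the MTD. But the Primary outcome escalation sentence requires that nobody has had a treatment-related grade ≥3 event, so read literally it blocks escalation. The article does not say what happens then.

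**The case against.** The strongest defence is that the intent can be read from context. Study design invokes the classic 3 + 3, and its escalation clause speaks of toxicity rather than of any adverse event. It is an overview; Primary outcome is the operational section and plainly counts people. There the treatment-related escalation sentence comes first, so the two sentences after it may simply be shorthand for the same kind of event, and the MTD sentence refers to the DLT window. This makes a participant-level, related-only count a likely intention. It does not settle the matter: the MTD sentence borrows the window but not the relatedness criterion, no sentence uses the defined term DLT as the quantity counted, and nothing says which wording governs. Condensing a protocol into an article explains missing detail, not two printed rules that disagree.

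Two stronger readings are tempting, and the documents do not support either.

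- A reader might infer that Data management and analysis supplies a further, rival MTD rule. It does not. It describes a summary, already counts participants and sets no threshold. It only needs aligning.
- A reader might infer that the any-cause wording turns a near-zero chance of wrongly stopping into a very large one. With no related toxicity and unrelated risk of 10%, 20% or 30%, the participant formula does give 33%, 75% or 94% over four levels. But those risks are not in the documents, and the comparator is not near zero. A DLT is judged against the trial intervention, and attribution covers radiosurgery as well as sulfasalazine, so radiosurgery effects and events merely judged possible still count. At 5% such risk the related-only rule stops about 10% of the time, and at 10% about 33%.

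**Conclusion.** The inconsistency is in the current text and affects the primary endpoint. On unit of count, Study design and Primary outcome disagree. On attribution, the DLT definition and escalation sentence disagree with the expansion and MTD sentences, and the late-event trigger in DMC oversight is also unqualified. Scenarios A to C establish this without any assumed rate. The size does rest on assumptions: taking 10% related risk at every level, the chance of stopping somewhere moves from about 33% to 43–55% if events are counted, and to 54–92% if unrelated events count at 5–20% risk. These figures show how far the readings can diverge; they do not predict this trial. It should be corrected because it governs the primary endpoint and costs little to put right. Which rule is clinically appropriate is not judged here.

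**What to change.** Reconcile Study design, Primary outcome, DMC oversight, and Data management and analysis into one rule, stated once and cross-referenced elsewhere. It should:

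- fix the unit of count, the attribution requirement and the time window
- use the protocol's own defined term, DLT, consistently for escalation, expansion and the MTD
- state what follows 1 of 6

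The sponsor decides which rule governs. For reporting, make the number of participants with a DLT at each dose level the primary summary, and tabulate grade 3 or higher events of any cause separately. The cost is a wording amendment, with no extra participants or procedures.

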To ensure adequate safety maturation, a minimum of 1 week must elapse after the completion of treatment on Day 3 in the preceding participant before the next participant is enrolled. Missed doses, dose reductions and early discontinuation will not remove a participant from DLT evaluability. Hospitalization does not remove a participant from DLT evaluability unless it is due to a pre‑planned elective procedure or expected disease progression rather than an adverse event related to sulfasalazine or GKRS. Serious adverse events (SAEs) will be reported according to regulatory timelines. Late radiation‑related toxicity will be monitored at 3, 6, 9 and 12 months post-GKRS, but will not influence dose‑escalation decisions.

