#### DMC oversight

The independent Data Monitoring Committee (DMC) conducts a scheduled safety review 1 week after completion of treatment in the third participant of each cohort. This timing is considered adequate for capturing clinically relevant early grade ≥3 drug‑related adverse events as sulfasalazine is administered for only three days, has a plasma half‑life of approximately 12.7 h, and is known to cause early rather than delayed toxicity. However, any grade ≥3 adverse events occurring after the initial review within the DLT window will trigger an additional DMC assessment during which enrollment will be paused. Such events may result in cohort expansion or dose de‑escalation as appropriate.

In accordance with standard practice in phase I trials combining systemic agents with radiotherapy, late toxicities will not contribute to dose‑escalation decisions because they occur too long after investigational drug exposure to inform MTD determination. Nevertheless, clinically meaningful late radiation‑induced adverse effects, including those potentially modified by radiosensitization and typically emerging months to years after treatment, will be documented and monitored throughout longitudinal follow‑up

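### The MTD and recommended phase II dose are fixed as the level below an exceeded one without requiring six participants there, so they will usually rest on 0 of 3

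*Protocol article*

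**What the plan says.** The Study design section expands a cohort to six after a single event of grade 3 or higher. It says that two or more events at a level "define that dose as exceeding the maximum tolerated dose (MTD), with the preceding dose as the recommended phase 2 dose". The Primary outcome section repeats the rule: the MTD "is defined as the dose preceding that at which 2 of 3 or 2 of 6 patients" have such an event within the DLT window. It also says: "Dose escalation follows the 3 + 3 design and proceeds only if no participant experiences" a treatment-related event of grade 3 or higher. No sentence says what follows 1 event in 6.

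De-escalation is announced in Study design ("The dose will be escalated or de-escalated with diminishing fractions of the preceding dose"), but the MTD rule makes no use of it. DMC oversight gives it a role only for events that arise after the one-week review and inside the DLT window: "Such events may result in cohort expansion or dose" de-escalation, as appropriate. No number to be treated at the lower dose is given.

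Under Sample size, with four levels, "the study is expected to enroll between 12 and 24 patients". Data management and analysis states: "The primary endpoint will be determination of the maximum tolerated dose and the recommended phase II dose".

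**The concern.** The only stated trigger for six participants in the escalation rules is one event at that same level. A level passed at 0 of 3 therefore stays at three. When the next level fails, the rule makes the three-participant level the MTD and recommended dose with no further check. That dose is the trial's primary result and the one carried into phase II, in patients whom the Study rationale section describes as possibly more susceptible to adverse effects.

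Two smaller gaps belong to the same rule. The escalation sentence in Primary outcome does not cover 1 of 6. And if 1.5 g is itself exceeded, the rule points to a preceding dose that does not exist.

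**Working it through.** **Inputs.** Four levels (1.5, 3, 4.5, 6 g), cohorts of 3 to 6, and the decision rules above. The documents give no DLT rates, so every rate p below is an assumption.

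**1. The plan's own figure.** 4 × 3 = 12 and 4 × 6 = 24 reproduce the stated enrolment. The 24 needs six participants at every level, so a level must be passable at 1 of 6. If only 0 of 3 permitted escalation, the maximum would be 3 + 3 + 3 + 6 = 15. The lower figure of 12 leaves every level, including the declared one, at three.

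**2. How often the declared dose has three participants.** A level is passed with probability s(p) = (1−p)³ + 3p(1−p)² × (1−p)³. Given that it is passed, the share with only three treated is 1 / (1 + 3p(1−p)²):

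| p | 3p(1−p)² | Share on three |
|---|---|---|
| 0.1 | 0.243 | 80% |
| 0.2 | 0.384 | 72% |
| 0.3 | 0.441 | 69% |
| 0.4 | 0.432 | 70% |

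With rising rates the share is 74% (0.1/0.2/0.3/0.4), 77% (0.05/0.1/0.2/0.4) and 75% (0.1/0.3/0.5/0.6). These shares are conditional on a level above 1.5 g being exceeded. Over all trials:
- At 10% throughout, that happens with probability s − s⁴ = 0.906 − 0.674 = 0.232, so the share of all trials is 0.232 × 0.805 = 19%.
- With 0.1/0.3/0.5/0.6 it is 0.900 × 0.753 = 68%.

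**3. What three participants show.** Exact (Clopper-Pearson) two-sided 95% upper limits for the DLT rate are 70.8% for 0/3, 45.9% for 0/6 and 64.1% for 1/6.

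**4. What six at the preceding level would change.** With six always treated, a level is accepted with probability P(at most 1 of 6), which is 0.233 at p = 0.4 and 0.109 at p = 0.5. The table gives the chance that 4.5 g is declared below an exceeded 6 g.

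| Assumed rates | As written | Six at 4.5 g |
|---|---|---|
| 0.1/0.2/0.4/0.5 | 0.906 × 0.709 × 0.309 × (1 − 0.172) = 16.4% | 0.906 × 0.709 × 0.233 × (1 − 0.172) = 12.4% |
| 0.1/0.3/0.5/0.6 | 0.906 × 0.494 × 0.172 × (1 − 0.082) = 7.1% | 0.906 × 0.494 × 0.109 × (1 − 0.082) = 4.5% |

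If six are also required at 6 g, some trials step back from 6 g to 4.5 g:
- 0.1/0.2/0.4/0.5: 0.906 × 0.709 × 0.233 × 0.125 × 0.5 = 0.9%
- 0.1/0.3/0.5/0.6: 0.906 × 0.494 × 0.109 × 0.064 × 0.648 = 0.2%

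With both rules in force the chance of declaring 4.5 g is therefore 13.3% and 4.7%, a fall of about 3 and 2 points.

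**5. The separate 6 g rule.** With 0.05/0.1/0.2/0.4, 6 g is the only level at 40%. Its chance of being recommended falls from 0.973 × 0.906 × 0.709 × 0.309 = 19.3% to 0.973 × 0.906 × 0.709 × 0.233 = 14.6%. With 0.1/0.2/0.3/0.4 it falls from 9.8% to 7.4%. As the top level, 6 g can never be a preceding dose, so these gains come wholly from requiring six there.

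**6. Sample size.** Mean N as written against both rules: 12.9 v 15.2 (10% throughout), 10.7 v 12.3 (20% throughout), 11.6 v 13.8 (0.1/0.2/0.3/0.4), 13.4 v 15.8 (0.05/0.1/0.2/0.4), 9.8 v 12.0 (0.1/0.3/0.5/0.6) and 11.1 v 13.3 (0.1/0.2/0.4/0.5). The maximum stays at 24. The minimum when all four levels open becomes 3 + 3 + 3 + 6 = 15.

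**The case against.** Naming the level below the exceeded one is a coherent rule, and filling it to six is an added safeguard. The article condenses a full protocol and cites a source for a classic 3 + 3, so the back-fill, and what happens if 1.5 g fails, may be set out there. Limitations already admits imprecise safety estimates. The gain is a few points, and 64% (1 of 6) is not far below 71% (0 of 3). The fix also shifts selection downward: with 0.1/0.3/0.5/0.6, choice of the 30% level (3 g) falls from 37.1% to 33.8% and choice of 1.5 g rises from 45.8% to 50.6%.

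Most of this stands as a limit on size. It does not remove the point. The article gives a complete definition of the MTD twice, and its lower figure of 12 fits a rule without back-fill. If the full protocol does require six, the article mis-states it. The general remark on precision does not tell a reader that the recommended dose may rest on three people.

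Two stronger readings are tempting. From the sentence that escalation proceeds only if nobody has an event, a reader might infer that every declared dose rests on three participants. The maximum of 24 contradicts this, since that reading caps enrolment at 15. A reader might also credit the preceding-level rule with the fall of nearly 5 points from 19.3% to 14.6%, but that belongs to the 6 g rule.

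**Conclusion.** The point holds as a weakness in the primary decision rule, worth correcting but moderate in size. If 1 of 6 permits escalation, as the maximum of 24 implies, a declared dose resting on 0 of 3 is the usual result once a level above 1.5 g is exceeded: about 70 to 80% of such trials, and 19 to 68% of all trials, over the assumed rates. The upper limits in step 3 depend on no assumed rate. Requiring six lowers the chance of recommending 4.5 g at a true rate of 40 to 50% by about 2 to 3 points with both rules in force (16.4 to 13.3%, 7.1 to 4.7%). The preceding-level rule by itself gives 4.0 and 2.6 points.

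**What to change.** In Study design and Primary outcome, state:
- Escalation follows 0 of 3 or at most 1 of 6.
- When a level is exceeded, return to the level below. If only three were treated there, treat three more. Declare it the MTD and recommended dose only if at most 1 of 6 has a DLT; otherwise step down again.
- If 1.5 g is exceeded, no MTD is declared.
- As a separate rule, if 6 g is not exceeded, treat six there before recommending it.

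In Sample size, change 12 to 15 for the case where all four levels open; 24 stands.

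**Cost.** About two more participants on average (1.6 to 2.4 in the scenarios above), up to three per step back, the downward shift in dose noted above, a protocol amendment, and one more DMC review per step back. On time, "a minimum of 1 week must elapse after the completion of treatment on Day 3 in the preceding participant" before the next enrolment. With Monday admission, Day 3 is a Thursday; seven days later is the next Thursday, so admissions fall two weeks apart and three participants need at least six weeks. At 24 patients in the planned 24 months, three would take about three months.

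The Specifications table says consent was obtained, and Table 1 reports spectral-quality values, so participants may already have been treated. If the cohorts are complete, the remedy costs nothing: report DLTs over number treated with the exact interval at the recommended dose, and call that dose provisional if only three were treated.
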